#### Fatigue

Fatigue is assessed by the Multidimensional Fatigue Inventory 20 (MFI-20), which is a 20-item self-assessment questionnaire measuring subjective fatigue perceived by patients according to the following sub-scales: general fatigue, physical fatigue, mental fatigue, reduced motivation and reduced activity [32, 33]. Each subscale uses a 5-point Likert scale ranging from 1 (strongly agree) to 5 (strongly disagree). A higher total score indicates a higher level of fatigue.

#### Pain

The Brief Pain Inventory short form (BPI-SF) is a self-administered questionnaire used to evaluate pain severity and pain interference [34]. The pain severity factor consists of four items that require patients to measure the severity of their current pain on a scale of 0 to 10 in order to capture the worst, average, and least pain intensity they felt in the previous 24 h. A value of “0” indicates “no pain” while “10” indicates “pain as bad (excruciating) as patients can imagine”. Pain interference involves 9 items on general activity, mood, walking ability, normal work, relationships with other people, sleep and enjoyment of life, rated on a numerical scale from 0 = “Does not interfere” to 10 = “Interferes completely”. The scale comprises a diagram of a human figure for locating areas of pain, questions about pain medications and the percentages of pain relief achieved with medications in the last 24 h.

#### Biological variables

Blood samples are drawn by venous puncture for analysis inflammatory variables.

Then, plasma is separated by centrifugation (at 4 °C, at a speed of 3500 rpm for 15 min), and transferred into plastic tubes of 2 mL. These tubes are frozen at -20 °C for a maximum of 3 months, then kept at -80 °C until analysis. C-reactive protein (CRP), interleukin 6 (IL-6), tumor necrosis factor alpha (TNF-α) are measured by immune nephelometry method.

#### Cardiorespiratory fitness

Patients perform a maximal graded exercise test (GET) on a cycle ergometer (Ergoselect 200; Ergoline; Bitz, Germany), under the supervision of a cardiologist. After a warm-up period of 3 min at 30 watts, intensity gradually increases by 10 watts every minute until exhaustion (V˙O_2_ peak). Pedaling frequency is maintained around 50 rpm. The exercise is interrupted when two of the three maximum criteria are reached: a decrease of cadence below 50 rpm, a respiratory exchange ratio value exceeding 1.0, attainment of 100% of age-predicted maximal HR (220-age). As soon as the maximum effort is reached, an active recovery period of 10 min without intensity is carried out.

Before, during exercise and recovery, HR is recorded using multichannel electrocardiograms (ECGs) (CASE P2, GE Healthcare, Buckinghamshire, UK). Ventilatory parameters are recorded continuously in real time, cycle by cycle with a gas analyzer system (MGC-CPX System; MGC Diagnostics Corporation, Saint Paul, MN, USA), which is calibrated using gases of known concentration. Oxygen uptake (V˙O_2_), carbon dioxide production (V˙CO_2_), respiratory exchange ratio (V˙CO_2_/V˙O_2_), and ventilation per minute (V˙E) are followed and monitored.

The ventilatory threshold 1 (VT_1_) and 2 (VT_2_) are determined, blinded according to the method of Wasserman using respiratory oxygen (V˙E⁄V˙O_2_) and carbon dioxide equivalents (V˙E⁄V˙CO_2_). The VT_1_ corresponds to the first increase in V˙E⁄V˙O_2_ without a concomitant increase in V˙E⁄V˙CO_2_, whereas VT_2_ corresponds to the second increase in V˙E⁄V˙O_2_ and the first increase in V˙E⁄V˙CO_2_ [35]. VT_1_ and VT_2_ are used as intensity of work for training. Perceived exertion is evaluated by the Borg Rating of Perceived Exertion (RPE) scale, from the beginning to the end of the graded test.

Before, at maximal effort and after 5 min recovery, blood gas (SaO_2_, PaO_2_, PaCO_2_, pH and Excess Bases) and lactate levels are collected using a micro-prick on the earlobe (EML105 Radiometer, Radiometer Medical Aps, Brønshøj, Denmark). These samples are analyzed using the RapidPoint® 500 system (Siemens Healthcare Diagnostics, Erlangen, Germany).

Systolic and diastolic blood pressures are monitored at rest and throughout the trial until the end of recovery, using an automatic sphygmomanometer (SunTech Tango+, Sun Tech, Morrisville, NC, USA).

#### Supervised exercise program

The supervised exercise program is performed on a cycle ergometer, for 3 sessions of 45 min per week for 12 weeks. It consists of an interval training exercise that starts with a 5-minute warm-up (intensity equal to ½ VT_1_), followed by 7 successive training session alternating 4 min of moderate work (intensity equal to VT_1_) and 1 min of intense work (intensity equal to VT_2_). An active recovery is performed for 5 min (at ½ VT1) (Fig. 3). Workloads are alternately readjusted by 10 watts to maintain target HR over time. HR is monitored by a pulse oximeter and fatigue by a visual analogue scale.

**Fig. 3 Fig3:**
[figure not shown]
Supervised exercise program

#### Follow-up of physical activity

From T0 to T6, physical activity level is followed using a Steel HR watch (Withings, Issy-les-Moulineaux, France), connected to the “Withings Health Mate” application on a mobile phone. The instructor downloads the “Withing Health Mate” mobile application and synchronizes it with the watch. He/she then gives information to the patient on how to use the watch and the mobile application. The application needs to be regularly used by the patients to transfer activity data via Bluetooth. All patients have to wear the watch from the time they get up until they go to bed. They have to schedule each session of physical activity practiced (e.g., walking, muscle strengthening, running, swimming, cycling), during which the distance, duration, intensity, maximum and average HR are collected. The watch also records the number of steps and calories burned, and the daily distance. All data are exported via the application.

## Statistical analyses

### Sample size

To detect a difference of TST of 10% compared to baseline value (considering a TST of 420 min), between the two groups, at T3, a Z-test with a type I error of 5% and a statistical power of 80% will be used. A total of 57 patients including 29 in CG and 28 in TG are required.

Two interim analyses for the efficacy and futility using the Lan-Demets method (O’Brien Fleming boundaries) to estimate the alpha spending function will be performed at 33% and 66% of the information fraction (after enrolment of 19 and 38 evaluable patients). With 10% of non-evaluable patients, 64 patients should be randomized. The primary objective will be done in modified intention-to-treat (miTT): all randomized and evaluable patients for the TST at T0 and T3.

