### Randomization

At T1, patients are randomly assigned (in a 1:1 ratio) to one of the two groups, namely either to receive standard oncological care alone (Control Group: CG) or standard care plus an exercise program (Training Group: TG), which starts at the halfway point through the chemotherapy protocol. During the follow-up period (T3-T6), both groups follow standard oncological care without supervised PA. Furthermore, the level of PA, without guidelines, is assessed by a connected watch.

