### Data analysis

Statistical analyses will be performed with SAS v9.4, and R v4.1. All primary statistical analyses will be conducted on the miTT population. A p-value < 0.05 will be considered statistically significant for the primary and secondary endpoints.

Patient characteristics will be described for all demographic and clinical data recorded at inclusion in the overall population, miTT population and according to group. Qualitative variables will be described with absolute numbers and percentages. Continuous variables will be reported using mean, standard deviation (SD), median, quartile 1-quartile 3 (q1-q3), min-max.

The comparison of average total sleep time for primary endpoint will be performed with Z-test. Comparisons for secondary endpoints will be carried out using Student’s t-test, Wilcoxon rank-sum test, analysis of variance (ANOVA), and Kruskall-Wallis test, as appropriate. The association of qualitative variables will be carried out using chi-square or Fisher’s exact tests, as appropriate.

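### A Z-test with an estimated SD at 19, 38 and 57 patients does not hold the stated 5% type I error, most of all at the first efficacy look

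*Protocol article*

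**What the plan says.** The Sample size section of the protocol article plans the trial on the statement that "a Z-test with a type I error of 5% and a statistical power of 80% will be used". It gives the target as follows: "To detect a difference of TST of 10% compared to baseline value (considering a TST of 420 min), between the two groups, at T3". It then states: "A total of 57 patients including 29 in CG and 28 in TG are required". The same section sets two interim analyses for efficacy and futility by the Lan-DeMets method with O'Brien-Fleming boundaries, "after enrolment of 19 and 38 evaluable patients".

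The Data analysis section repeats the choice for the analysis: "The comparison of average total sleep time for primary endpoint will be performed with Z-test". Student's t-test appears in the next sentence, for secondary endpoints only. The section also sets the significance rule: "A p-value < 0.05 will be considered statistically significant for the primary and secondary endpoints".

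No SD for TST appears in the sample size text. The only mention of an SD in the statistical sections is descriptive: "Continuous variables will be reported using mean, standard deviation (SD), median, quartile 1-quartile 3 (q1-q3), min-max".

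**The concern.** A Z-test refers the standardised difference to the normal distribution, which is exact only when the SD is known. Here it will come from the data: about 10 against 9 patients at the first look, 19 against 19 at the second, and 29 against 28 at the end. The standardised difference then follows a t distribution with heavier tails.

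With one analysis of 57 patients this would hardly matter. The interim looks make it matter more. O'Brien-Fleming boundaries lie far out in the tail early on, where normal and t probabilities differ most in relative terms, and the first boundary is applied to the smallest sample. The departure always favours rejection, so an early efficacy stop would rest on a weaker standard than the spending function promises.

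**Working it through.** **Inputs from the article.** Type I error 5%, power 80%, 57 evaluable patients (29 and 28), 1:1 allocation, looks at 19 and 38, Lan-DeMets spending of O'Brien-Fleming type, and a difference of 10% of 420 min = 42 min.

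**Assumptions, because the article does not state them.** Two-sided test; 42 min read as the absolute difference between arms at T3; SD pooled across arms; normally distributed TST; arm sizes of 10/9 and 19/19 at the interims. Futility rules were not modelled because their form is not given.

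**The plan's own figure.** N = 57 cannot be reproduced independently, because the SD is missing. It can only be solved backwards. With a two-sided, single-look Z formula,

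SD = 42 / [(1.960 + 0.842) × √(1/29 + 1/28)] = 42 / (2.802 × 0.2649) ≈ 56.6 min.

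A one-sided formula implies 63.8 min. The allowance for non-evaluable patients does reproduce: 57 / 0.90 = 63.3, rounded up to 64.

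**Boundaries.** The spending function on each side is α(t) = 2[1 − Φ(2.241/√t)], where 2.241 is the normal quantile for 0.025/2. At t = 19/57, 38/57 and 1, the cumulative one-sided error spent is 0.00010, 0.00605 and 0.02500. Solving the joint normal probabilities gives |z| bounds of 3.710, 2.511 and 1.993.

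**Level at each look.** The intended level is 2[1 − Φ(c)]. The level with an estimated SD is 2·P(t > c) on n − 2 degrees of freedom (df).

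| Patients | df | Bound c | Intended | With estimated SD | Ratio |
|---|---|---|---|---|---|
| 19 | 17 | 3.710 | 0.00021 | 0.00174 | 8.4 |
| 38 | 36 | 2.511 | 0.0120 | 0.0167 | 1.38 |
| 57 | 55 | 1.993 | 0.0463 | 0.0512 | 1.11 |

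**Overall type I error.** Simulation of the three looks under no effect (2 million trials):

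- SD known, normal bounds: 4.99%
- SD estimated, normal bounds: 5.80%
- SD estimated, t-quantile bounds at the same nominal levels: 5.03%

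The first line shows that the boundaries themselves are sound. The excess of 5.80 − 4.99 ≈ 0.8 points comes from pairing normal critical values with an estimated SD. A single analysis at 57 patients would give 2·P(t > 1.960) = 5.51% on 55 df. If the design were one-sided at 5%, the three-look figure would be 5.57%.

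**Power** (at the back-solved SD of 56.6 min, d = 42/56.6 = 0.742).

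| Procedure | Single analysis | Three looks |
|---|---|---|
| Z-test as written, SD estimated | 79.8% | 79.5% |
| t-test | 78.6% | 78.0% |

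If N = 57 was instead sized with the interim looks taken into account, the implied SD is 56.2 min, and the three-look figures become 80.1% (Z) and 78.6% (t). A single-look t-test at SD 56.6 min reaches 80% with 59 patients.

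**The case against.** The best defence is that this is a condensed article. It does not say how the variance is obtained, which critical values apply at each look, or whether the test is one- or two-sided. The bounds used above are derived and appear nowhere in the text, and the name Z-test may only describe the sizing and boundary calculation. This tempers the point without removing it: the Data analysis section assigns the Z-test to the primary comparison itself and, in the next sentence, gives Student's t-test to the secondary endpoints. The two tests are distinguished, and no known SD is offered.

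The size of the effect is also a fair objection, and it stands. The eightfold ratio at the first look is a rise from 0.02% to 0.17%, about 0.15 percentage points, and the overall excess is below one point.

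Two stronger readings are tempting, but the document does not support them.

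- A reader might infer that the 80% power is wrong as well. It is not, for the test as written: the slightly loose cut-off offsets the estimated SD, and power stays near 80%. The figure of 78 to 79% belongs to the replacement t-test and depends on an SD solved backwards from N = 57.
- A reader might apply the general p < 0.05 rule literally at the final look and report an error of about 6.2%. That adds a separate question, whether the final threshold is adjusted for the interims, and the extra should not be charged to the Z-test.

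**Conclusion.** The point holds for the type I error. The Z-test named for the primary endpoint, used with an estimated SD and normal O'Brien-Fleming bounds, gives about 5.8% overall against the stated 5%. The per-look levels are 0.0017 instead of 0.0002, 0.0167 instead of 0.0120, and 0.0512 instead of 0.0463. The conclusion rests on a two-sided 5% design, a pooled SD, normal data and normal critical values at each look. A one-sided design leads to the same conclusion at 5.57%.

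The fault is real and runs towards false positives, but it is small. It should be fixed before any interim analysis; it does not undermine the design. It gives no ground for calling the stated power wrong.

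**What to change.** In both the Sample size and Data analysis sections, replace the Z-test for the primary endpoint with a t-based test at every look, and apply the Lan-DeMets spending function to its p-values.

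- For an unadjusted two-sample t-test on 17, 36 and 55 df, the critical values become about 4.70, 2.645 and 2.04, in place of 3.71, 2.51 and 1.99.
- If a baseline-adjusted model is chosen, use that model's df. With one covariate these are 16, 35 and 54, and the first bound is about 4.77. Adjustment is optional and is not needed to correct this fault. What it would gain in power depends on a correlation between baseline and T3 that the article does not give.
- State whether the test is one- or two-sided, and recompute the bounds if the actual looks do not fall at exactly 19 and 38 patients.
- Restate the power. If 57 came from a two-sided, single-look Z formula (SD about 56.6 min, an assumption), the t-test has about 78 to 79%.

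The cost is a change of wording and a loss of 1 to 2 points of stated power. The type I error returns to about 5.0% with no more patients. Keeping 80% on the single-look reckoning would take 59 evaluable patients instead of 57, or 59 / 0.90 = 65.6, so 66 randomised instead of 64.

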### Data analysis

Statistical analyses will be performed with SAS v9.4, and R v4.1. All primary statistical analyses will be conducted on the miTT population. A p-value < 0.05 will be considered statistically significant for the primary and secondary endpoints.

Patient characteristics will be described for all demographic and clinical data recorded at inclusion in the overall population, miTT population and according to group. Qualitative variables will be described with absolute numbers and percentages. Continuous variables will be reported using mean, standard deviation (SD), median, quartile 1-quartile 3 (q1-q3), min-max.

The comparison of average total sleep time for primary endpoint will be performed with Z-test. Comparisons for secondary endpoints will be carried out using Student’s t-test, Wilcoxon rank-sum test, analysis of variance (ANOVA), and Kruskall-Wallis test, as appropriate. The association of qualitative variables will be carried out using chi-square or Fisher’s exact tests, as appropriate.

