**Methods:**

This multicenter, randomized clinical trial evaluate the effectiveness of a moderate to high intensity physical activity program (45 min, 3 times per week), lasting 12 weeks, in minimizing insomnia, sleep disturbances, anxiety/depression, fatigue, and pain, and in enhancing cardiorespiratory fitness. Patients with breast cancer be recruited from six hospitals in France and randomly allocated to either the “training” or the “control” group. Baseline assessments include questionnaires [Insomnia Severity Index (ISI), Pittsburgh Sleep Quality Index questionnaire (PSQI), Hospital Anxiety Depression Scale (HADS), Epworth Sleepiness Scale (ESS)], home polysomnography (PSG), and 7-day actigraphy coupled with completion of a sleep diary. Assessments are repeated at the end of training program and at six-month follow-up.

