### Secondary endpoints

Secondary endpoints are a decrease of insomnia severity, an improvement in sleep quality, a decrease in sleepiness, anxiety/depression, pain, fatigue, inflammatory variables, and an enhancement of cardiorespiratory fitness.

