#### Anxiety and depression

Patients complete the Hospital Anxiety and Depression Scale (HADS) [24]. This scale is a 14-item self-report instrument with 7 questions related to anxiety and 7 others to depressive symptoms. The answer format offers four response options, which are scored with values ranging from 0 to 3 (0 = not at all to 3 = nearly all the time). Thus, each subscale (depression and anxiety) yields a score values between 0 and 21. HADS defines three ranges for both scales: 0–7 (no symptoms), 8–10 (doubtful symptomatology), and 11–21 (some symptomatology). It is possible to calculate a HADS total score by summing the anxiety and depression items [25].

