Furthermore, we propose a supervised endurance training program that alternates moderate and high intensities, with personalized target intensities, adjusted according to the physical characteristics of the subject. This type of training has already been proposed to patients presenting cardiovascular disease or metabolic syndrome [58–61], with a growing body of evidence emerging in cancer patients [16]. Training has been associated with many benefits, such as improving physical functioning and fitness (i.e., V˙O_2_ peak), reducing side effects of cancer treatments, preventing bone loss and weight gain, increasing muscle strength, decreasing cancer-related fatigue and improving quality of life [16, 62–66].

While exercise is safe and well tolerated by patients undergoing cancer treatments or in the rehabilitation phase [67], findings also show that knowing, and managing insomnia with physical activity offers interesting therapeutic prospects for cancer treatment. However, most studies use only questionnaires without recording objective sleep using polysomnography [57, 68].

This clinical trial will provide additional evidence regarding the effectiveness of physical exercise during chemotherapy in minimizing insomnia, improving sleep quality, reducing fatigue, pain, anxiety, increasing cardio-respiratory fitness and health-related quality of life. If shown to be effective, exercise intervention programs could be welcome addition to the standard program of care offered to patients with breast cancer.

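### All secondary endpoints are judged at the same unadjusted p < 0.05 as the primary, with no gating on the primary and no exploratory label

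*Protocol article*

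**What the plan says.** The Data analysis section gives a single significance criterion: "A p-value < 0.05 will be considered statistically significant for the primary and secondary endpoints". It then names the tests to be used for secondary endpoints, each applied as appropriate, and mentions no adjustment.

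The Secondary endpoints section lists the family: "Secondary endpoints are a decrease of insomnia severity, an improvement in sleep quality, a decrease in sleepiness, anxiety/depression, pain, fatigue, inflammatory variables". These are seven domains. Better cardiorespiratory fitness closes the list and makes 8. Some of them hold more than one variable:

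- Under Biological variables, "C-reactive protein (CRP), interleukin 6 (IL-6), tumor necrosis factor alpha (TNF-α) are measured".
- Under Anxiety and depression, "each subscale (depression and anxiety) yields a score values between 0 and 21".
- Under Pain, the inventory is "used to evaluate pain severity and pain interference".

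The Abstract describes the trial as evaluating the programme's effectiveness "in minimizing insomnia, sleep disturbances, anxiety/depression, fatigue, and pain, and in enhancing cardiorespiratory fitness". The closing paragraph of the Discussion says: "This clinical trial will provide additional evidence regarding the effectiveness of physical exercise during chemotherapy in minimizing insomnia, improving sleep quality, reducing fatigue, pain, anxiety".

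The only control of type I error described in the article is the alpha spending for the interim analyses, in the Sample size section. The 5% type I error given there belongs to the comparison of total sleep time (TST).

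**The concern.** The criterion is a stated decision rule and not a gap left for a later document. It gives each secondary endpoint the same standing as the primary: any of them that falls below 0.05 may be called statistically significant, whatever happens to TST.

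With 8 or more such tests, at least one significant result is fairly likely even if exercise changes none of these outcomes. By the count below, 8 of the 12 scores are self-reported, and patients allocated to supervised cycling or to standard care alone know which they received. The planned number of evaluable patients is 57. A reader of the results would have no pre-stated basis for telling a chance finding from a confirmed effect, while the Abstract and Discussion present these outcomes as evidence of effectiveness.

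**Working it through.** **The plan's own figure.** The article states no family-wise error rate for the secondary endpoints, so there is nothing to reproduce. It gives no sidedness, test count or correlation for them either. Those are assumptions here, shown over a range.

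**Count of tests.**

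- Lower count: one test per listed domain, m = 8.
- Score-level count: ISI (1), PSQI (1), ESS (1), HADS anxiety and depression (2), BPI-SF severity and interference (2), MFI-20 total (1), CRP, IL-6 and TNF-α (3), peak oxygen uptake (1). Sum: 1 + 1 + 1 + 2 + 2 + 1 + 3 + 1 = 12. The Study outcomes section schedules all of these at T3. The first eight, from ISI to MFI-20, are self-reported.

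**Independent tests, all nulls true, two-sided 5% each.**

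- Any false significant result: 1 − 0.95^m. For m = 8, 1 − 0.95^8 = 0.337. For m = 12, 1 − 0.95^12 = 0.460.
- False result in the favourable direction only (2.5% per test): 1 − 0.975^m. For m = 8, 1 − 0.975^8 = 0.183. For m = 12, 1 − 0.975^12 = 0.262.
- Expected number of false significant results, at any correlation: 8 × 0.05 = 0.4 and 12 × 0.05 = 0.6.

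**Correlated tests.** The model takes m standard normal statistics with common correlation ρ, c = 1.96, and φ and Φ as the normal density and distribution function.

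- Either direction: 1 − ∫ φ(u) [Φ((c − √ρ·u)/√(1−ρ)) − Φ((−c − √ρ·u)/√(1−ρ))]^m du
- Favourable direction: 1 − ∫ φ(u) [Φ((c − √ρ·u)/√(1−ρ))]^m du

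Numerical integration gives:

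| Quantity | m | ρ = 0 | ρ = 0.5 | ρ = 0.8 |
|---|---|---|---|---|
| Any false significant result | 8 | 33.7% | 25.0% | 15.7% |
| Any false significant result | 12 | 46.0% | 31.9% | 18.6% |
| False benefit | 8 | 18.3% | 12.5% | not computed |
| False benefit | 12 | 26.2% | 16.0% | not computed |

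At ρ = 0.7 the false-benefit figures are 9.5% (m = 8) and 11.6% (m = 12).

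**Benchmarks.** A single two-sided 5% test has a 5% chance of a false result in either direction and 2.5% in the favourable one. At ρ = 0.5 the inflation is the same on both scales: 25.0/5 = 12.5/2.5 = 5.0 for 8 tests, and 31.9/5 = 16.0/2.5 = 6.4 for 12. At ρ = 0.8, either direction, it is still 15.7/5 = 3.1 for 8 tests.

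**Sensitivity to sidedness.** If the tests were one-sided at 5%, the chance of a false benefit at ρ = 0.5 would be 21.9% (m = 8) or 27.0% (m = 12), against 5% for a single test.

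**With control.** A Bonferroni level of 0.05/8 = 0.00625 gives 1 − (1 − 0.00625)^8 = 4.9% for 8 independent tests.

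**The case against.** The strongest reply is that this is a condensed article. Adjustment or ordering of secondary tests is often left to the statistical analysis plan, and a nominal 0.05 for secondaries is common practice. One primary endpoint is named and powered, and calling the others secondary already sets them apart. This stands in part: the absence of a multiplicity method would not by itself be a point. But the article goes further and fixes the criterion for calling a secondary result significant. A gate or an exploratory label in an unseen plan would sit awkwardly with that sentence, which would still need changing.

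Several stronger readings are tempting, and the article does not support them:

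- **That the chance of a false benefit claim is 25% to 32% instead of 5%.** Those figures count false results in both directions. With two-sided tests and the same assumptions, false benefit is about half that, and its benchmark is 2.5%.
- **That the plan breaks a promised 5% rate.** The 5% is attached to TST. No family-wise rate is promised for the secondaries.
- **That the family runs to two dozen tests or more.** The polysomnography and actigraphy lists include TST itself and descriptive items such as bedtime, and those lists are not called secondary endpoints. The Study outcomes section schedules at T6 only objective sleep, melatonin and temperature, with activity tracking, although the Abstract says assessments are repeated at six months. No larger count can be itemised with confidence.
- **That the sponsor would claim success on a secondary if TST fails.** The rule permits it, but the article does not say so. The Discussion wording is general prose and not a decision rule.

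**Conclusion.** The point holds as a modest, inexpensive improvement. The article judges 8 domains, or about 12 scores, at the same unadjusted 0.05 as the primary, without gating or an exploratory label. With two-sided tests and every secondary null true, the chance of at least one false significant result in either direction is about 25% to 32% at an assumed correlation of 0.5, and 16% to 46% over correlations from 0.8 to 0. A false benefit has a chance of about 12.5% to 16% at correlation 0.5. If exercise truly affects some of these outcomes, fewer nulls are true and the rates are lower.

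The secondary tests do not change the type I error of the primary endpoint, so the main conclusion of the trial is not at risk from this. Whether 0.05 suits the primary's own final analysis after interim looks is a separate question.

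**What to change.** Change the sentence in Data analysis so that the claim of statistical significance applies to the primary endpoint only. State that secondary endpoints are reported as exploratory: group differences with 95% confidence intervals, and any p-values marked as unadjusted.

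If the sponsor wants confirmatory claims on some secondaries, it should pre-specify a short ordered sequence, tested only if the primary is significant and stopped at the first non-significant result. Everything outside the sequence stays exploratory. Which endpoints enter, and in what order, is for the sponsor to decide, because the article does not rank them. Since the trial may stop at an interim look, the level used for the sequence should be stated for each look at which it could be tested.

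The cost is one or two sentences in the protocol and analysis plan, with no extra patients or data. The downside is that secondaries outside such a sequence, or all of them if the primary is not significant, can no longer be claimed as statistically significant.

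### The p < 0.05 rule for the primary endpoint conflicts with the O'Brien-Fleming alpha spending that the same plan uses to hold a 5% type I error

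*Protocol article*

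**What the plan says.** Two sections of the protocol article set the rule for the primary endpoint, total sleep time (TST).

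- **Sample size.** The error rates are fixed by "a Z-test with a type I error of 5% and a statistical power of 80% will be used". The size is given as "A total of 57 patients including 29 in CG and 28 in TG are required". The same section schedules "Two interim analyses for the efficacy and futility using the Lan-Demets method", with O'Brien-Fleming boundaries, at 33% and 66% information, that is, after 19 and 38 evaluable patients.
- **Data analysis.** The threshold is "A p-value < 0.05 will be considered statistically significant for the primary and secondary endpoints".

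The second statement covers the primary endpoint by name. It does not refer back to the boundaries or distinguish interim from final looks. The article gives no adjusted final level. It also does not say whether the test is one- or two-sided, which form of the O'Brien-Fleming spending function is meant, or whether the futility rule is binding.

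**The concern.** A spending function divides one 5% budget among the looks. Any part spent on efficacy at 19 and 38 patients must be missing from the final analysis, so the final nominal level has to be below 0.05. The Data analysis section keeps 0.05.

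The trial therefore has two published rules for the same test. They agree for most results and disagree for a final p just below 0.05, where one section declares success and the other does not. If that happens, the choice of rule would be made, or appear to be made, after the result is known.

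**Working it through.** **Inputs from the documents.** Type I error 5%; 57 evaluable patients; looks at 19, 38 and 57; Lan-DeMets spending of O'Brien-Fleming type; final threshold 0.05.

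**Assumptions where the article is silent.** Two-sided test (one-sided shown as a variant); futility non-binding; information proportional to evaluable patients.

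**The plan's own figures.** 57/3 = 19 and 57 × 2/3 = 38, so the looks match the stated fractions. 57/0.9 = 63.3, rounded up to the stated 64. The 57 itself cannot be reproduced because no standard deviation is given, but the boundaries depend only on the information fractions, so this does not affect the check.

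**Step 1: alpha spent.** With 2.5% spent per side, the two-sided cumulative spend at information t is

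2 × 2[1 − Φ(z₀.₉₈₇₅/√t)], with z₀.₉₈₇₅ = 2.241.

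- t = 1/3: 2.241/0.577 = 3.88, spend 0.0002
- t = 2/3: 2.241/0.816 = 2.75, spend 0.0121
- t = 1: spend 0.0500

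**Step 2: boundaries.** Solve in turn for the critical value at each look so that the cumulative crossing probability under the null equals the spend. The look statistics are multivariate normal with correlation √(tᵢ/tⱼ).

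| Look | t | Boundary z | Nominal two-sided p |
|---|---|---|---|
| 1 | 1/3 | 3.710 | 0.0002 |
| 2 | 2/3 | 2.511 | 0.0120 |
| Final | 1 | 1.993 | 0.0463 |

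**Step 3: keep 0.05 at the end.** Replace 1.993 by 1.960 and leave the interim boundaries alone. The cumulative error is the interim spend plus the probability of crossing for the first time at the final look: 0.0121 + 0.0414 = 0.0535.

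**Step 4: variants.**

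| Reading | Final nominal p needed | Cumulative error if 0.05 is kept |
|---|---|---|
| Two-sided, 2.5% spent per side | 0.0463 | 5.35% |
| Same, fractions 0.33 and 0.66 | 0.0464 | 5.34% |
| Two-sided, function applied to the whole 5% | 0.0439 | 5.56% |
| One-sided 5% | 0.0451 | 5.45% |

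Every variant puts the required final level below 0.05. Only the exact value depends on what the article leaves open.

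**The case against.** The best reply is that the Sample size section already names the controlling method and the 5% error. The 0.05 sentence is then a generic statement of overall alpha, and exact boundaries are normally left to a statistical analysis plan. That is fair as to the boundary values, and their absence is no fault. It does not rescue the sentence. The sentence sets a p-value cut-off for the primary endpoint by name, so it is a misstatement rather than an omission. An analysis plan carrying the right boundaries would contradict the published rule.

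A second reply carries more weight. The excess over 5% assumes that futility stops may be overridden. If they are binding, some false positives are lost and the excess can vanish. With illustrative binding stops at z < 0 and then z < 0.5, which are not the protocol's, the error in favour of training falls from about 2.7% to about 2.5%. The article does not say which applies, so the inflation is conditional. The conflict between the two thresholds remains.

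Three stronger readings are tempting, and the documents do not support them:

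- **That 0.05 applies at all three looks.** This would give about 10.7% two-sided, but the Sample size section expressly assigns O'Brien-Fleming boundaries to the interims.
- **That the final test by itself exceeds 5%.** Taken alone, a final test at 0.05 has a 5% error. Only the cumulative error over the three looks is above it.
- **That every secondary endpoint needs a multiplicity adjustment.** The article does not say that each subscale is a separate confirmatory test. Its Discussion describes these symptoms as a correlated cluster. Handling of secondary endpoints is commonly left to the analysis plan.

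**Conclusion.** The point holds as a wrongly stated decision threshold for the primary endpoint. Under two-sided testing with non-binding futility, the rule as written has a cumulative type I error of about 5.35% (5.56% under the other spending form) against the stated 5%. That is an excess of 0.35 to 0.56 percentage points. The final level consistent with the Sample size section is about 0.046 (0.044), and the two sections give opposite answers for a final p between that level and 0.05.

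The numerical effect is modest and conditional on those assumptions. The correction is still needed, because the formal interim design exists to hold 5% and the later sentence undoes it at the final look. Any further error from using a Z-test with an estimated standard deviation is a separate matter, which this correction would not remove.

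**What to change.** In Data analysis, limit the 0.05 sentence to the secondary endpoints and add a sentence for the primary endpoint along these lines: *The primary endpoint is tested at each look against the Lan-DeMets O'Brien-Fleming boundary at the actual information fraction, for an overall type I error of 5%.* State in the same place whether the test is one- or two-sided and which form of the spending function is used. The levels can be given as an example: two-sided 0.0002, 0.0120 and 0.0463 if 2.5% is spent per side at 1/3, 2/3 and 1. They should not be fixed as constants, because they change with sidedness, spending form and the actual timing of the looks. Saying whether futility is binding would complete the rule.

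The cost is a short wording change and a slightly stricter final threshold. If 57 patients give 80.0% power with a single two-sided look, the design with the correct boundaries at all three looks has about 79.5%. No added patients or procedures are needed to make the two sections agree.
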